### Measurements

#### Energy, protein, and ONS intake

All parameters are assessed continuously until discharge or for a maximum of 30 days (Table 2). The RDs calculate daily energy and protein requirements according to relevant current clinical nutrition guidelines that apply to the patients in the MEDPass Trial [10, 14, 33]. The formula per patient is chosen according to age and body mass index (BMI). As some patients may suffer from progressive renal failure, the Clinical Practice Guideline of the National Kidney Foundation is used to calculate these patients’ protein needs [34]. The formulas for daily energy requirements as related to the primary outcome are listed in Table 3.

**Table 3 Tab3:** Calculation of daily energy requirements

Formulas for daily energy requirements		
	BMI < 18.5 kg/m^2^	BMI > 18.5 kg/m^2^
< 65 years	Actual body weight × 30 kcal [10]	Actual body weight × 27 kcal [10]
> 65 years	Actual body weight × 32 kcal [14]	Actual body weight × 30 kcal [14, 33]

Recommended protein intake is calculated according to the guidelines for geriatric and medical patients using the formula 1 g/kg body weight/day [10, 14, 33]. However, patients with chronic kidney disease and estimated glomerular filtration rate (eGFR) < 30 mL/min/1.73m^2^, who are not on dialysis, are an exception. In this case, the actual body weight is multiplied by 0.8 g/kg body weight/day [34].

Detailed data concerning food intake is assessed after every meal. Each component of every meal is evaluated separately by the personnel collecting the tray after the meal. More specifically, the consumed percentage (100%, 75%, 50%, 25%, or 0%) of any delivered food component is evaluated and the value is noted accordingly on the meal card. Furthermore, after each meal, patients are interviewed on food intake between the main meals. To keep track of intake in addition to meals, a separate document is used. It is distributed and collected during morning meal rounds. All food intake documentation is temporarily stored at ward level and collected daily by the RDs from Monday to Friday. For the weekends, it is collected on Mondays. If data points are missing, the RDs interview the patient directly to fill the respective data gaps. All meals at the facility are prepared according to recipes of the Bern University Hospital database. Energy and protein intakes are primarily calculated via the electronic menu system LogiMen® (Kretschmer-Keller Leonberg, Germany, 2016, version 5.4). The system contains energy and protein content data for all hospital meals and snacks. This method ensures high calculation accuracy as the recipes are integrated in the system. Energy and protein intake from food items that are not registered in the LogiMen® system are calculated by the RDs using nut.s nutritional software® (dato Denkwerkzeuge, Vienna, Austria, 2008, version 1.32.74). All meal cards and calculations are sent to one of the co-investigators, who is blinded to patient allocation, for recalculation.

The amount of ONS consumed is monitored daily by the RNs by measuring the amount consumed with a measuring cup. In the trial setting, ONS is prescribed and listed in the medication chart in the EHR. All medications are listed with the amount prescribed. The amount consumed is documented on a standardized basis for all medications. The consumed amount is documented in the EHR with an accuracy of ± 5 ml. From this assessment, the RDs calculate energy and protein intake from ONS.

#### Handgrip strength

Handgrip strength is assessed by the RDs on study visits 2–6 (Table 2) until discharge or for a maximum of 30 days (Table 2). Handgrip strength is evaluated using the JAMAR® Hydraulic Hand Dynamometer (Patterson Medical, Warrenville, IL, USA) with an accuracy of ± 0.5 kg. The measurement is always conducted according to the same procedure and on the same hand. If possible, the measurement is performed on the dominant hand. To ensure data validity, the measurement is taken three times with a break of at least 30 s between measurements and the highest value is noted [35].

#### Body weight

Body weight is monitored as part of standard clinical practice by the nursing staff with an accuracy of ± 0.1 kg. Immobile patients are weighed on the seca® wheelchair scale (Vogel & Halke, Germany, model 665) and mobile patients on the sitting scale seca® (Vogel & Halke, Germany, model 959). Body weight measurements are prescribed by the MDs according to the study schedule (Table 2) directly after patient enrolment in the trial. RDs evaluate if body weight measurements are accurate according to the patient’s clinical status and medications. RDs may contact the MDs to discuss the validity in case of uncertainty.

#### Appetite and nausea

The course of appetite and nausea are recorded by the RDs during weekly study visits (Table 2). The level of appetite and nausea on the current day are the focus of the assessment. The assessment is carried out by asking the patient to scale the level of appetite/nausea using a visual analog scale (VAS). The scale visible to the patient only has smileys. The scale on the backside of the smiley scale ranges from 0 to 10 cm so that the subjective measurement can be objectified with an accuracy of ± 0.1 cm.

#### Hospital LOS and 30-day mortality

One of the co-investigators evaluates hospital LOS and 30-day mortality after the participants are released from the hospital or after 30 days of trial inclusion respectively (Table 2). Hospital LOS is assessed from the EHR as number of days: the calculation excludes the day of hospital discharge [36]. Hospital LOS is only assessed in medical inpatients since the geriatric inpatients have a prefixed duration of stay. Assessment of 30-day mortality is done by phone call to the patients’ home or the institution where the patient was referred to. If the patient is still hospitalized, the information is available in the EHR.

#### Baseline patient characteristics and procedural variables

The following baseline patient characteristics are recorded by RDs during visit 1 (Table 2):
✓ Disease categories for main diagnosis (gastrointestinal disease, infectious disease, cardiovascular disease, neurological disease, oncologic disease, other diseases)✓ Department in which the patient is hospitalized✓ Gender (male, female)✓ Age (years)✓ Energy content per ml ONS (1.5 kcal/ml or 2 kcal/ml)✓ NRS 2002 total score✓ NRS 2002 subscore for impaired nutritional status✓ Body weight (kg)✓ Body height (cm)✓ BMI (kg/m^2^)

The following procedural variables are recorded after discharge by one of the co-investigators:
✓ Number of days from trial inclusion to hospital discharge✓ Number of days with prescribed ONS✓ Number of days with energy and protein intake monitoring✓ Compliance versus non-compliance with the study protocol✓ Number of meals at which patients were nil per os during energy and protein intake assessment (meals at which patients are not allowed to eat for medical reasons)✓ Number of meals at which food intake could not be assessed✓ Involvement of RDs in the treatment of the patients

#### Safety outcomes

As defined by Good Clinical Practice (GCP) [27], SAEs are monitored and investigated continuously. Potential SAEs in this trial are pneumonia caused by ONS aspiration and death associated with pneumonia caused by ONS intake in the MEDPass-mode.

### Statistical analysis

#### Hypothesis

##### Working hypothesis

We hypothesize that patients in the intervention group (MEDPass mode) consume more energy as compared to patients in the control group.

##### Null hypothesis (Ho)

There is no difference in energy intake between the groups.

#### Sample size calculation

Based on our clinical experience, we assumed for our power analysis that administration of ONS in the MEDPass mode increases energy intake (primary endpoint) by at least 10% (i.e., by 200 kcal from an average of 2000 kcal/day). Furthermore, we assumed that an average patient weighs 75 kg and therefore has an approximate energy requirement of 2200 kcal. A final assumption is that in current clinical practice they may only receive 2000 kcal/day. Therefore, to demonstrate that intervention group patients have an increased average daily energy intake of 200 kcal/day (i.e., from 2000 (SD 500 kcal) to 2200 (SD500 kcal)), we need to include 200 patients to achieve 80% power (alpha error of 0.05). The power calculation used the sampsi command in STATA® (Stata Corp, USA, 2017, version 15.3). Importantly, this trial is not powered to investigate whether the difference in energy intake of 200 kcal/day makes a significant difference to clinical outcomes. However, a similar increase in energy intake has previously shown to decrease the risk of adverse outcome and mortality [7].

#### Primary analysis

The baseline patient characteristics will be summarized for both groups. The primary analysis will be performed as an intention-to-treat (ITT) analysis including all randomized patients regardless of protocol adherence. In a further step, we will also do a per-protocol analysis excluding patients with major protocol violations as outlined below.

For the primary outcome, we will test whether MEDPass administration is superior to usual care and compare the average amount of daily energy intake using a Student’s *t* test or chi-square test. We will also fit linear regression models adjusted for initial NRS 2002 score and average amount of energy in the ONS, reported adjusted differences (coefficients), and corresponding 95% confidence intervals (CIs). Total energy, protein, and ONS intake throughout the study period will be divided by days of assessment per patient. Linear regression analysis adjusted for stratification factors will also be used for the evaluation of average daily protein intake as compared to the individual requirement (%) throughout the hospitalization, average intake of ONS/day (ml) throughout the hospitalization, and hospital LOS (days) between the groups. Logistic regression analysis adjusted for stratification factors will be is used for difference in 30-day mortality (yes/no) between the groups. Repeated measure models will be used for the evaluation of differences in course of handgrip strength throughout the hospitalization, weight changes throughout the hospitalization, and course of appetite and nausea throughout the hospitalization. The procedural variables will be analyzed and presented descriptively. There will not be a statistical safety assessment since there are no safety endpoints in the MEDPass Trial. Safety events will be presented descriptively.

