**Methods:**

The MEDPass Trial is a randomized, controlled, open-label superiority trial. Patients in the MEDPass group receive 50 ml of ONS four times per day, distributed with the medication rounds. Patients in the control group receive ONS between meals. The primary outcome is average daily energy intake (% of calculated daily requirement). For our power analysis, we assumed that administration of ONS in the MEDPass administration mode increases energy intake by at least 10% (i.e., by 200 kcal for an average energy requirement of 2200 kcal/day). Thus, with the inclusion of 200 patients, this trial has 80% power to demonstrate that intervention group patients have an average intake of 2200 kcal/day (SD 500 kcal) versus 2000 kcal/day (SD 500 kcal) in control group patients. Energy and protein intakes from ONS and all food consumed are monitored continuously throughout the hospital stay and are statistically compared to the patient’s requirements. Secondary outcomes include average daily protein intake (% of calculated daily requirement), average intake of ONS/day, the course of body weight, handgrip strength, appetite, and nausea. Furthermore, hospital length of stay and 30-day mortality are assessed. The primary statistical analysis will be performed as an intention-to-treat analysis adjusted for the stratification factors used in randomization.

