## Methods

### Study design

The MEDPass Trial is a randomized, controlled, clinical trial (RCT) conducted with parallel groups. Blinding of patients is not possible because of the evident differences in ONS administration times. Therefore, it is conducted as an open-label RCT. The MEDPass Trial is a superiority trial. The allocation ratio of intervention group and control group is 1:1.

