### Randomization

Randomization is stratified according to the NRS 2002 total score and the energy content of the ONS (kcal/ml). The NRS 2002 total score is stratified as NRS 3, NRS 4, or NRS 5-7. The energy content of the ONS is stratified as either 1.5 kcal/ml or 2 kcal/ml. Even distribution of these factors between the groups minimizes bias since they may directly influence primary and secondary outcome parameters. Randomization is conducted using the Research Electronic Data Capture (REDCap®) program (Vanderbilt University, Nashville, TN, USA, 2020, version 9.1.15). Registered Dietitians (RD) input the stratification data and randomize electronically within the REDCap® program. The RDs do not have access to the concealed randomization sequence. The randomization list with random numbers for coding was pre-specified by the Clinical Trial Unit (CTU) Bern and electronically integrated into the REDCap® database.

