The stratification of randomization is aimed at preventing statistical differences between groups due to ONS energy density. This is a relevant approach since differences between groups would directly affect the primary outcome. Furthermore, the stratification for NRS 2002 score is aimed at reducing differences in nutritional risk between groups. This may reduce bias significantly and therefore all statistics will be adjusted for both stratification factors. The wide selection of ONS available in the institution represents daily clinical practice. There is no influence of the financial sponsor on the selection of ONS in this study.

Our initial calculation and projections predicted the completion of patient recruitment in spring 2020. In the course of the trial, recruiting was prolonged for various reasons, including predominantly organizational barriers to recruitment. Organizational barriers are frequently described as significant for the prolongation of clinical trials [40–42]. In patients with unscheduled admissions, such as the majority of those in our facility’s medical department, recruitment challenges are more evident. LOS in the medical department is usually shorter than on the geriatric wards. This disqualifies some of the medical patients because after screening and referral, they may not stay three more days as needed according to the eligibility criteria. Moreover, medical patients with unscheduled hospitalizations may be too anxious about their treatment, in pain, or too unwell to provide consent [42]. Recruitment on the geriatric wards also presents challenges. Reading and understanding the consent forms may be difficult for some of the patients [41]. Furthermore, distrust and/or fatigue are known barriers in recruiting elderly patients onto clinical trials [41].

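### The decisive primary analysis is not fixed: the statistics section tests superiority with an unadjusted t test or a chi-square test, while the abstract and discussion promise a stratification-adjusted analysis

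*Protocol article*

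**What the plan says.** Three parts of the protocol article describe the primary analysis, and they differ.

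- **Primary analysis section.** This is the only place that names the tests. The superiority comparison of mean daily energy intake is attached to a Student's t test or a chi-square test, and regression follows as an addition: "test or chi-square test. We will also fit linear regression models adjusted for initial NRS 2002 score". The second covariate there is worded as the average energy amount of the supplement.
- **Abstract, Methods.** "The primary statistical analysis will be performed as an intention-to-treat analysis adjusted for the stratification factors used in randomization".
- **Discussion.** The authors expect the stratification to reduce bias, "therefore all statistics will be adjusted for both stratification factors".

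On the design: "Randomization is stratified according to the NRS 2002 total score and the energy content of the ONS (kcal/ml"), with NRS 2002 in three classes (3, 4, 5-7) and energy density in two (1.5 or 2 kcal/ml). The Randomization section adds that these factors may act directly on the outcomes. The Outcomes section gives the primary outcome as average daily energy intake, in kcal and as % of requirement. It is continuous on either scale.

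**The concern.** A superiority trial needs one analysis whose result decides. Here the section that should fix it offers two unadjusted tests and one adjusted model, and two other sections give precedence to the adjusted model. Three problems follow.

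1. If the t test and the adjusted model fall on opposite sides of 0.05, the text does not say which counts.
2. A chi-square test cannot compare means. It needs intake to be cut into categories, and no cut-off is defined. Left in the plan, it is an undefined extra route to a significant result.
3. The regression covariate is not clearly the randomization factor. Randomization used the energy density of the product. The average energy amount of the supplement could be read as energy supplied or consumed. That is measured after randomization and can be changed by the administration mode, so adjusting for it would distort the treatment coefficient.

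**Working it through.** **Inputs from the protocol.** "we need to include 200 patients to achieve 80% power (alpha error of 0.05"); a difference of "200 kcal/day (i.e., from 2000 (SD 500 kcal) to 2200 (SD500 kcal")); "The allocation ratio of intervention group and control group is 1:1". Sidedness is not stated. I take two-sided because the null hypothesis reads "There is no difference in energy intake between the groups".

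**Inputs assumed.** The documents do not give the share of outcome variance explained by the strata (R²), so I use 0 to 0.30. The simulation (4,000 trials per setting) also assumes six strata, permuted blocks of 4 and additive stratum effects.

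**Step 1. Reproduce the sample size.** n per arm = 2 × (1.960 + 0.842)² × 500² / 200² = 98.1, rounded up to 99, or 198 in total. The plan's 200 is reproduced. A one-sided test would need 156 and does not reproduce it. With 100 per arm, SE = 500 × √(2/100) = 70.7 and power = Φ(200/70.7 − 1.96) = Φ(0.868) = 80.7%. The stated size is therefore that of an unadjusted two-sided comparison of means.

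**Step 2. t test against adjusted model.** Under stratified randomization the true standard error of the mean difference is about 70.7 × √(1 − R²), while the t test keeps using about 70.7.

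- Actual size of the t test = 2 × [1 − Φ(1.96/√(1 − R²))]
- Power of the t test = Φ((200 − 1.96 × 70.7) / (70.7 × √(1 − R²)))
- Power of the adjusted model = Φ(200 / (70.7 × √(1 − R²)) − 1.96)

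| Assumed R² | t test, type I error | t test, power | Adjusted, power |
|---|---|---|---|
| 0 | 5.0% | 80.7% | 80.7% |
| 0.05 | 4.4% | 81.4% | 82.7% |
| 0.10 | 3.9% | 82.0% | 84.6% |
| 0.20 | 2.8% | 83.4% | 88.5% |
| 0.30 | 1.9% | 85.0% | 92.2% |

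Simulation agrees. At R² = 0.10 the t test has 3.8% type I error and 81% power, against 5.1% and 84% adjusted. With a true 200 kcal effect, the two disagree on significance in 0.4% (R² = 0), 2.7% (0.10) and 7.9% (0.30) of trials.

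**Step 3. Cost of leaving the choice open.** Simulated type I error if the most favourable result is taken:

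| Assumed R² | Better of t test and adjusted model | Best of these two and chi-square at 2200 kcal |
|---|---|---|
| 0 | 5.6% | 8.5% |
| 0.10 | 5.1% | 7.5% |
| 0.30 | 4.8% | 6.7% |

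Monte Carlo error is about √(0.05 × 0.95/4000) = 0.3 percentage points. The first column is 5% within that error or close to it. The excess comes from the chi-square option.

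**Step 4. Power of a chi-square test.** Cut intake at an assumed 2200 kcal, the average requirement in the Sample size calculation. The proportions above the cut are 1 − Φ(200/500) = 34.5% (control) and 50.0% (MEDPass). With 100 per arm and pooled proportion 0.422, power = Φ((0.155 × √100 − 1.96 × √(2 × 0.422 × 0.578)) / √(0.345 × 0.655 + 0.25)) ≈ 61%. Reaching 80% would take 316 patients. Depending on how much individual requirements vary between patients, power lies at about 50-62%.

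**The case against.** The strongest reply is that little is at stake. The t test is valid after stratified randomization, it matches the sample size calculation, and it keeps at least the planned 80% power at every R² examined. The adjusted model is already specified with coefficients and confidence intervals. The two tests nearly coincide, so choosing between them hardly moves the error rate. The chi-square wording is probably a stock phrase: the sentence compares an average, the regression is linear, and no responder endpoint appears anywhere. The covariate wording may also just be loose, since the next regression sentence, on the other outcomes, speaks of stratification factors.

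Most of this stands and limits the size of the point. It does not remove it. The Abstract and the Primary analysis section give different answers in current text, so an analysis plan that is not shown would have to depart from one of them. A test that does not fit the outcome is still named for it.

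A reader might infer more than the documents support:

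- **That the t test inflates type I error or leaves the trial underpowered.** It does neither. Its loss is relative to the adjusted model and vanishes if the strata are not prognostic.
- **That type I error reaches about 11%.** That figure also counts the choice between kcal and % of requirement, which is a separate matter of outcome definition, and it needs an assumed spread of individual requirements.
- **That a responder analysis is planned.** None is defined. The 50-62% power figures show only what a chi-square test would deliver at an assumed cut.

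**Conclusion.** The point holds as an internal contradiction about which analysis is confirmatory, together with a test that does not fit the outcome and a covariate that does not match the randomization factor. Its numerical size is modest. Between the t test and the adjusted model the type I error stays near 5%. The price of the unadjusted test is conservatism and a few points of power, conditional on an R² that the documents do not give. With chi-square left available the type I error could reach about 7-9%, conditional on an assumed cut-off and on selecting the most favourable result. The sample size is not in error. Adjustment for the two strata leaves power at 80.7% if they explain nothing and raises it otherwise.

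**What to change.** In the Primary analysis section, replace the sentence naming the t test and chi-square test, and the regression sentence after it, with wording such as:

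*The primary analysis is an intention-to-treat linear regression of average daily energy intake (on the one scale declared primary, kcal or % of calculated requirement) on randomized group, with NRS 2002 stratum (3, 4, 5-7) and ONS energy-density stratum (1.5 or 2 kcal/ml) as categorical covariates. The treatment coefficient with its 95% confidence interval and two-sided p value at 0.05 is the confirmatory result. An unadjusted t test is a sensitivity analysis.*

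Delete the chi-square test for this outcome. The density stratum entered must be the one used at randomization, replacing the covariate now worded as an average energy amount. This brings the section into line with the Abstract and the Discussion.

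The cost is a wording amendment before database lock, with no new data and no change to the 200 patients.

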### Outcomes

The primary outcome is the average energy intake/day (kcal, % of calculated daily requirement). Secondary outcomes include average protein intake/day (g, % of calculated daily requirement), average ONS intake/day (ml), the course of handgrip strength (kg), body weight (kg), appetite, and nausea. Furthermore, hospital LOS and 30-day mortality are assessed.

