**Fig. 1 Fig1:**
[figure not shown]
Patients’ flow. NRS 2002, Nutritional Risk Screening 2002; ONS, oral nutritional supplement; RD, registered dietitian; SAE, serious adverse event

**Table 2 Tab2:** Time schedule for participants

Study period	Screening	Intervention period					Evaluation	Follow-up
Visit	1	2	3	4	5	6		
Day	0	1	8	15	22	29	*	**
NRS 2002 total score	x							
NRS 2002 subscore nutritional status	x							
Inclusion and exclusion criteria	x							
Information, informed consent	x							
Assignment to study group		x						
Baseline patient characteristics		x						
Energy intake/day (kcal)**		Continuous assessment						
Protein intake/day (g)**								
ONS intake/day (ml)**								
Serious adverse events (SAE)**								
Handgrip strength (kg)		x	x***	x***	x***	x***		
Body weight (kg)		x	x***	x***	x***	x***		
Body height (cm)		x						
BMI (kg/m^2^)		x						
Appetite (VAS)		x	x***	x***	x***	x***		
Nausea (VAS)		x	x***	x***	x***	x***		
Procedural variables							x	
Hospital LOS (d)							x	
30-day mortality (y/n)								x

*After patient dismissal or after 30 days of inclusion

**For 30 days upon inclusion

***Assessment at day 1, day 8, day 15, day 22, and day 29

Visits 2–6: study visits may be conducted earlier or later by a maximum of 2 days

The criteria for ONS discontinuation are:
ONS is not indicated anymore due to increased food intakeOccurrence of a serious adverse event (SAE) that necessitates a halt to the prescription

The reasons for discontinuation are documented. Furthermore, withdrawal from the trial is possible at any time at the patients’ request.

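### The adjusted primary-outcome regression omits baseline body weight, which is collected on every patient and sets the denominator of the percentage outcome: a forgone precision gain, not an error in the stated power

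*Protocol article*

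**What the plan says.** The Outcomes section names the outcome on two scales: "The primary outcome is the average energy intake/day (kcal, % of calculated daily requirement"). The percentage needs a requirement, and Table 3 (Energy, protein, and ONS intake) sets it as actual body weight times 27, 30 or 32 kcal according to age and BMI class. One cell, for example, reads "Actual body weight × 30 kcal".

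Table 2 schedules body weight on day 1, and the list of baseline characteristics includes it. Every patient with a percentage value must therefore have a weight.

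The Primary analysis section first names a Student's t test or chi-square test and then continues: "We will also fit linear regression models adjusted for initial NRS 2002 score and average amount of energy in the ONS". The abstract describes the primary analysis as adjusted for the stratification factors, and the Discussion says all statistics will be adjusted for both. Those factors are NRS 2002 (3, 4, or 5-7) and ONS energy density (1.5 or 2 kcal/ml). Body weight appears in no stated adjustment set.

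**The concern.** On the percentage scale the outcome is intake divided by a multiple of weight. If intake rises less than proportionally with weight, light patients score high and heavy patients low in both arms, and weight predicts the outcome. If intake is proportional to weight, the division removes weight from the percentage, but weight then predicts the kcal value. So weight should be prognostic on at least one of the two listed scales. A model without it leaves that variance in the residual.

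The article stratifies on its two factors because they may directly influence the outcomes, and weight meets that test at least as clearly. There is also reason to doubt exact proportionality: every MEDPass patient is offered the same 4 × 50 ml = 200 ml, or 300 to 400 kcal at 1.5 to 2 kcal/ml, whatever the patient weighs.

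At stake is precision for the trial's one primary comparison, from data already collected, in a trial that prolonged recruitment to reach its desired power.

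**Working it through.** **1. The plan's own figure.** The inputs come from Sample size calculation: "increased average daily energy intake of 200 kcal/day (i.e., from 2000 (SD 500 kcal) to 2200 (SD500 kcal")), and "we need to include 200 patients to achieve 80% power (alpha error of 0.05"). Study design gives 1:1 allocation. Sidedness is not stated. Two-sided is inferred from the null hypothesis ("There is no difference in energy intake between the groups") and because a one-sided test would need only 156.

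- n per arm = 2 × (1.960 + 0.842)² × 500² / 200² = 98.1, rounded up to 99, so 198 in total against the stated 200.
- Power with 100 per arm at d = 200/500 = 0.4 is 80.7% (normal approximation) or 80.4% (noncentral t, 198 df).

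The stated size is reproduced with no covariate gain assumed.

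**2. Model for the effect of weight.** Mean weight 75 kg and control intake 2000 (SD 500, so CV 0.25) are the plan's figures. The following are assumptions, because the article does not give them: lognormal weight with SD 10 to 18 kg; intake proportional to weight^b with total CV held at 0.25; one requirement factor for all (2200/75 kcal/kg); and a treatment effect of +10% of the control mean. Let v = (SD of weight / 75)².

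- CV² of the percentage outcome = 1.0625 × (1 + v)^(1 − 2b) − 1
- Correlation of weight with the percentage = [(1 + v)^(b − 1) − 1] / (CV of percentage × √v)
- Correlation of weight with kcal = [(1 + v)^b − 1] / (0.25 × √v)
- Unadjusted d = 0.10 / CV; adjusted d = unadjusted d / √(1 − r²)

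**3. One case in full: SD 15 kg, b = 0, percentage scale.**

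- v = 0.04; CV² = 1.0625 × 1.04 − 1 = 0.105; CV = 0.324; d = 0.309; power 58%.
- r = (1/1.04 − 1) / (0.324 × 0.2) = −0.593; r² = 0.352.
- Adjusted d = 0.309 / √0.648 = 0.383; power 77%.

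**4. Power without → with weight, percentage scale, 100 per arm**

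| SD of weight | b = 0 | b = 0.25 | b = 0.5 | b = 1 |
|---|---|---|---|---|
| 10 kg | 69% → 79% | 75% → 81% | 80% → 83% | no gain |
| 12 kg | 65% → 79% | 72% → 80% | 80% → 84% | no gain |
| 15 kg | 58% → 77% | 68% → 80% | 80% → 86% | no gain |
| 18 kg | 52% → 75% | 64% → 80% | 80% → 89% | no gain |

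Before rounding, the gain is 9.9 to 22.9 points at b = 0 and 2.7 to 8.3 points at b = 0.5.

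**5. Kcal scale.** Unadjusted power is 80.4% throughout. At SD 15 kg, adjustment gives 80.4%, 82%, 87%, 94% and above 99% for b = 0, 0.25, 0.5, 0.75 and 1.

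**6. Check with another model.** With normally distributed weight and a set correlation between kcal intake and weight, at SD 15 kg, power on the percentage scale goes from 55% to 77% at r = 0, from 71% to 82% at r = 0.3, and from 85% to 89% at r = 0.5. At SD 10 kg and r = 0.5 it stays at 89.9%. The pattern is the same.

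**The case against.** The strongest case against is that nothing in the plan is wrong here. Adjusting for the stratification factors alone is valid, and further prognostic covariates are often left to a statistical analysis plan. The validity stands. The second part stands less well, because the article does not leave the adjustment set open: it names the same two factors in the abstract, in Primary analysis and in the Discussion.

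A reader might infer that omitting weight takes the trial below its planned 80%. The documents do not support that. The calculation is for an unadjusted kcal comparison and holds on its own inputs. The 58% in the worked case comes from carrying an SD of 500 kcal over to a percentage scale that the article never powered, with an assumed spread of weight. It depends on which scale is primary as well as on the covariate; at b = 0, adjusting brings the percentage scale to 77%, still below the unadjusted kcal figure.

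A reader might also infer that being the denominator must leave weight in the error term. It need not: at b = 1 the division has already removed it.

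A third tempting reading is that chance weight imbalance biases the result. At SD 15 kg the standard error of the difference in mean weight is 15 × √(2/100) = 2.1 kg, so a gap of 3 kg or more in either direction arises in about 16% of trials. With b = 0 it would move the percentage by about 4% in relative terms (75/72 − 1). That variation is already reflected in the standard error and the alpha level. Adjustment would reduce it, but it is not bias.

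Finally, Primary analysis lists the t test or chi-square test first and the regression as an addition. If the unadjusted test is primary, adding a covariate to the regression leaves the primary test unchanged. That stands, and the fix has to deal with it.

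**Conclusion.** The point holds as an efficiency recommendation. Baseline weight is collected on everyone, it sets the denominator of the percentage outcome, and it is absent from the adjusted regression. Weight should predict the outcome on at least one of the two listed scales, so adding it should improve precision there.

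The amount cannot be determined from the documents. It ranges from nothing (percentage scale at b = 1, kcal scale at b = 0) to about 23 points of power (percentage scale, b = 0, SD 18 kg). Every figure above the plan's own 80% rests on the assumed SD of weight and the assumed relation of intake to weight.

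**What to change.** Before database lock, amend Primary analysis to prespecify that:

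- the linear regression for the primary outcome includes baseline body weight as a continuous covariate, using the value from which the requirement is computed, alongside the randomization strata (NRS 3, 4, 5-7; 1.5 or 2 kcal/ml), on whichever scale is primary;
- this adjusted regression is the primary test, as the abstract implies, in place of the unadjusted t test or chi-square test;
- average protein intake uses the same covariate, since its requirement is also a multiple of weight (1 or 0.8 g/kg).

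The cost is a short change of wording and one degree of freedom, with no new data or patients. The estimate becomes conditional on weight; in a linear model without interaction the treatment difference keeps its meaning.
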